##### Recruitment of older people

ACPs who are enrolled in the study and have completed the training to participate in the study (see ‘*Study procedure: training’)* will then screen and recruit people living with and without dementia, who are sequentially referred to them for a HMR. Eligibility for individual people living with and without a diagnosis of dementia include: aged 65 years and older who can speak English, are eligible for a HMR, and are able to provide informed written consent (patient or carer).

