##### Intervention

The Goal-directed Medication review Electronic Decision Support System (G-MEDSS) (accessible from gmedss.com) is a validated electronic platform (CCDSS) that has been designed to provide clinical decision support for healthcare practitioners (GPs and ACPs) when completing a medication review for their older patients, to provide person-centred care to meet their goals and preferences. The G-MEDSS platform was, developed, validated and evaluated in a previous study with ACPs, GPs and carers for people living with dementia, using mixed-methodology that informed the design and usability of the tools within the CCDSS [42]. The G-MEDSS is designed to produce patient-specific deprescribing reports for a patient’s GP.

The G-MEDSS contains three tools:
The Goals of Care Management tool allows the patient’s goals of care to be identified and aligned with their medication management strategies. The tool also allows for free-text information to be entered into the system.The Drug Burden Index Calculator© is a validated tool that identifies medications with anticholinergic and sedative effects (measured by the DBI) and provides information on a patient’s total exposure to these drug classes and their risks to older people [28, 31].The revised Patient’s Attitudes Towards Deprescribing questionnaire (rPATD) was developed and validated to explore people’s attitudes, beliefs, and experiences regarding the number of medications that they are taking, and how they would feel about ceasing one or more of their medications [34, 43]. Three different versions of the rPATD were incorporated into G-MEDSS to allow for selection as appropriate for the patient: a) older adult, b) caregiver, and c) people with cognitive impairment (rPATDcog) versions [35]. The psychometric properties of the rPATD were established in Australian older adults and carers, and has established face, content, criterion, construct and internal validity and test-retest reliability.

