#### Outcomes and follow-up

The primary outcome will be any reduction of anticholinergic and/or sedative medication use, as measured by DBI, between baseline and 3-months (binary outcome). Previous studies consistently observe an association between increasing DBI and impaired physical function [29]. The degree of exposure that results in a clinically significant change has been estimated to be a difference in DBI of approximately 0.5 [44]. Our previous study found that DBI is reduced in usual care HMR in 8.9% of patients by a median value of 0.28 [45], and an increase in this proportion by 10% was seen as a clinically meaningful effect on a population level. It was not feasible to power the study to primarily investigate impact on multifactorial measures of physical function.

Secondary outcomes will include:
Recommendations to reduce anticholinergic and or sedative medications as measured by DBI in the HMR report and/or the G-MEDSS report;Prevalence of deprescribing (cessation and/or dose reduction) any medicationChanges in clinical outcomes (physical function, cognitive function, falls, and institutionalisation)Changes in patient process outcomes (medication adherence and physician visits)Mortality at 3-monthsA subgroup analysis (of the above outcomes) for people living with and without dementia

All ACPs will be required to collect additional information of their HMR recipients at baseline (during HMR interview) and at a 3-month follow-up visit. The 3-month follow-up has been added exclusively to this study for the purposes of data collection as the HMR process (usual care) does not involve a follow-up visit. The following outcomes will be assessed of the patient participants enrolled in the study: medication adherence, cognitive impairment, functional status, falls, institutionalisation and the number of physician visits. Mortality data will be captured by the ACP participants at 3-month follow-up (Table 1).

**Table 1 Tab1:** Patient participant data to be collected during the study

	Measure (s)	Baseline^a^	3-months
Demographics			
Age		✓	
Sex		✓	
Ethnicity		✓	
Marital Status		✓	
Education Status		✓	
Geographic remoteness/locality	PhARIA	✓	
Medication Profile			
Current medication list (prescribed, OTC and complementary, regular or PRN)		✓	
Changes to medication list (e.g. additions, cessations, ↑↓dose)			✓
Ceased medications		✓	✓
Adherence	MGL	✓	✓
Attitudes towards deprescribing^b^	rPATD, rPATDCog	✓	
Anticholinergic and sedative burden	DBI	✓	✓

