Comorbidity and Physical Function			
Comorbidities	FCI	✓	✓
Cognition	Mini-Cog© [46]	✓	✓
Independent activities of daily living	NHCCSFSI	✓	✓
Physical Function	SPPB	✓	✓
Falls History		✓	✓
Others			
Institutionalisation (e.g. hospitalisation)		✓	✓
Physician visits (e.g. GP or specialist appointments)			✓
Mortality			✓
Goals of care^b^		✓	

^a^at the time of the HMR interview; ^b^only for patients in the intervention arm of the study

*PhARIA* The Pharmacy Access/Remoteness Index of Australia – quantifies degree of remoteness (geographic and professional) [47], *OTC* Over-the-counter, *PRN* when required, *MGL* Morisky, Green, Levine Scale [48], *rPATD* revised Patients’ Attitudes Towards Deprescribing [34], *rPATDCog* Revised Patients’ Attitudes Towards Deprescribing for people with Cognitive impairment [35], *DBI* Drug Burden Index [28], *FCI* Functional Comorbidities Index [49], *NHCCSFSI* National Home and Community Care Services Functional Screening Instrument [50], *SPPB* Short Physical Performance Battery [51], *GP* General practitioner

↑↓ = changes

The Morisky Green Levine Scale will be used to measure self-reported patient medication adherence [48]. Cognitive impairment will be assessed using the Mini-Cog© [46, 52–54]. The National Home and Community Care services Functional Screening Instrument (NHCCSFSI) (part one) and the Short Physical Performance Battery (SPPB) will be used to assess the functional status of patient participants [50, 51]. Details regarding scoring of these measures used in this study can be found in Additional file 1.

Data to calculate the Functional Comorbidity Index (FCI) will be collected from the patients. The FCI is a sum of 18 self-reported comorbid conditions with a score of 0–18. The FCI will also be used to measure comorbidities that predict physical function in older adults. A higher FCI score indicates greater morbidity and is associated with poorer physical function [49].

Falls (any fall in the last 12 months at baseline and number of falls at 3-months), institutionalisation (admission to hospital in the last 12 months at baseline and number of days admitted to hospital, nursing home or respite care at 3-months) and the number of physician visits (GP and specialist) will be captured over 3 months by providing patients and/or their carers a calendar to self-record events that will be collected by ACPs.

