#### Statistical analyses

The primary analyses will be conducted using an ‘intention-to-treat’ approach and will be reported according to the guidelines of the Consolidated Standards of Reporting Trials (CONSORT) 2010 statement. Descriptive statistics (means and proportions) will be used to report the demographics of the study populations (ACPs and patient participants) at baseline. Binary continuous and count outcomes will be analysed using logistic, linear and negative binomial regression models, respectively. All models will include a covariate for the intervention group, with a random effect for the clusters (ACPs). Analyses will provide an estimate of the difference between groups, 95% confidence intervals (CI) and *p*-values. All statistical tests will be two-tailed, and p-values of < 0.05 will be deemed statistically significant. Appropriate model checking will be conducted. The statistician performing the data analysis will be blinded to the identity of each treatment group.

Secondary analyses will include:
Where appropriate, to conduct further adjusted analyses, covariates will be included for the patients’ baseline value (for that outcome) and any baseline characteristic for which there is evidence of imbalance between intervention and comparison groups;A subgroup analysis for people living with dementia;For clinical outcomes, assessments of associations between change in DBI or a deprescribing of a medication, using the same statistical methods as described above, but with the intervention group removed from the model and replaced by change in DBI or deprescribing of medication;Association between rPATD and deprescribing in overall patient population.

To analyse the responses to the rPATD questionnaire, factor scores will be created for each of the 4 factors (appropriateness, burden, concerns about stopping and involvement) as previously described [34]. Likert responses to the global question ‘I would be willing to stop one or more of my medications if my doctor said it was possible’ will be dichotomised into those that agree (strongly agree and agree) and those that are unsure/disagree (unsure, disagree, strongly disagree). Factor scores and responses to the global questions will be compared to deprescribing outcomes (DBI and prevalence of deprescribing) using Mann-Whitney and χ^2^ tests.

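### The rPATD–deprescribing association is fixed as unadjusted Mann-Whitney and chi-square tests, which cannot hold medicine count, baseline DBI or the pharmacist cluster

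*Protocol article*

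**What the plan says.** The last item in the list of secondary analyses (protocol article, Statistical analyses) is: "Association between rPATD and deprescribing in overall patient population". The method follows in the paragraph on the questionnaire: "Factor scores and responses to the global questions will be compared to deprescribing outcomes (DBI and prevalence of deprescribing) using Mann-Whitney" and chi-square tests, with no covariate, stratification or cluster term. The same section applies a two-sided 5% threshold to all tests, so these results would be declared significant or not.

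Other analyses are treated differently. For the trial outcomes, "All models will include a covariate for the intervention group, with a random effect for the clusters (ACPs"), and the association of clinical outcomes with change in DBI or deprescribing uses those same methods with the group term replaced. Further adjusted analyses may add the baseline value of the outcome and "any baseline characteristic for which there is evidence of imbalance between intervention and comparison groups".

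Three other places matter:
- The Intervention section says that the rPATD explores attitudes, beliefs and "experiences regarding the number of medications that they are taking".
- Patients qualify if they are "aged 65 years and older who can speak English, are eligible for a HMR, and are able to provide informed written consent" (patient or carer). These study criteria set no minimum DBI or medicine count.
- Table 1 records "Current medication list (prescribed, OTC and complementary, regular or PRN") and DBI at baseline. It marks the rPATD as collected "only for patients in the intervention arm of the study".

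**The concern.** The exposure here is observational, so randomisation gives no protection, and balance between arms says nothing about who holds which attitude within an arm. If patients with longer medication lists score differently on the questionnaire (on the burden factor, for example) and also have more medicines that could be stopped, score and outcome will be associated even when attitude plays no part.

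The Background notes that the rPATD has not yet been trialled as a guide to deprescribing in a clinical setting. Readers are therefore likely to take a significant result as a sign that attitudes matter for what gets deprescribed, and the planned tests cannot separate that from the length of the medication list. They also treat patients of one pharmacist as independent, although the sample size section assumes an ICC of 0.07 for DBI reduction.

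**Working it through.** **The plan's own figures.** None is given for the rPATD analysis. The sample size section supplies the number of patients. For 20% versus 10%, 80% power and 5% two-sided, the size without clustering is 199 per arm. The design effect is 1 + (5 − 1) × 0.07 = 1.28, and 2 × 199 × 1.28 = 509, in line with the stated 500. The rPATD is collected in one arm, so about 500 / 2 = 250 patients can enter if the arms are equal.

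**Outcome side, from the design.** If each medicine has chance h of being stopped or reduced, a patient on M medicines has any deprescribing with probability 1 − (1 − h)^M. With h = 5% (assumed), M = 5 gives 1 − 0.95^5 = 23% and M = 15 gives 1 − 0.95^15 = 54%. For DBI reduction (taken as yes/no, as in the primary outcome), a patient with baseline DBI 0 is a certain "no".

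**Score side, assumed.** The only support in the documents is the content of the questionnaire. The correlation r between score and medicine count is therefore varied, including r = 0.

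**General simulation.** A confounder X has correlation r with the score and odds ratio OR per SD with deprescribing. Attitude has no effect, 20% are deprescribed, N = 250, and there are 1,500 data sets per setting with no clustering. Rejection rate of the unadjusted Mann-Whitney test at 5%:

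| r | OR 1.25 | OR 1.5 | OR 2.0 |
|---|---|---|---|
| 0 | 4.7% | 4.7% | 4.8% |
| 0.1 | 4.5% | 6.1% | 8.5% |
| 0.2 | 6.3% | 8.1% | 12.3% |
| 0.3 | 6.9% | 12.5% | 21.8% |
| 0.4 | 8.5% | 16.1% | 35.7% |

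The chi-square test on the dichotomised global item (about 75% agreeing, assumed) is less affected. At OR 2.0 it rejects in 5.7% at r = 0.1 and 18.9% at r = 0.4. Logistic regression that also holds X, run at OR 2.0, rejects in about 4–6% for r = 0.1 to 0.4.

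**Medicine-count simulation.** This uses the formula above with a mean of 8–12 medicines, h = 3–8% and N = 250, all assumed except N. Unadjusted rejection runs from about 6–10% at r = 0.1 to about 15–41% at r = 0.4. The spread of medicine count matters: in a separate run at r = 0.4, a Poisson spread gave 17–32% and an SD of 4–5 gave 28–50%. At r = 0 the rate stays near 5%, so including DBI-0 patients does not by itself create an association. A logistic model with log medicine count and baseline DBI, restricted to DBI above 0 for the DBI outcome, gave about 4–7%.

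**Does other text already adjust this?** The adjusted-analysis item selects covariates by the outcome's baseline value and by imbalance between randomised groups. The first could be read as bringing in baseline DBI, but a Mann-Whitney or chi-square test has no place for it. Medicine count would enter only if the arms happened to differ on it.

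**The case against.** The plan speaks of an association and makes no causal claim. In these simulations score and outcome really are associated, through medicine count, so a rejecting test is right about the marginal question it asks. The rates above are false positives only for the question of whether attitude matters given the medicines taken. For plain prediction, an unadjusted association is a legitimate answer. This stands: the risk is one of interpretation.

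A reader might infer more strongly that medicine count and baseline DBI drive the attitude scores, so that a positive finding would be spurious. The documents do not support that. They contain no data linking baseline DBI to rPATD scores. For medicine count they offer only what the questionnaire asks about, which makes a link plausible, mainly for burden and appropriateness, and less obviously for involvement, concerns about stopping or the global item.

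The inputs to the calculations are also assumptions, and with weak links almost nothing happens. The analysis stands last among the secondary analyses, and the Aims do not mention it.

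These points limit the size and severity. They do not answer why this association alone loses the regression and the cluster effect that the plan gives its other observational association.

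**Conclusion.** The point holds in a limited form, as a minor one. The protocol fixes tests that cannot account for medicine count, baseline DBI or the pharmacist, and no other text clearly repairs this. The outcome side of the confounding follows from the design; the score side is plausible but undocumented. The inflation, relative to no effect of attitude, is therefore unknown: nil with no correlation, close to nominal with a weak one, and large only if the correlation is near 0.4 and medicine count strongly affects deprescribing. It would be wrong to conclude that a significant result must be spurious. The supportable conclusion is that such a result could not be told apart from an effect of how many medicines there were to stop. The primary outcome analysis is unaffected.

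**What to change.** In the Statistical analyses section, make the main rPATD analysis the logistic model with a pharmacist random effect already specified there. Use the factor score or the dichotomised global item as exposure, and baseline medicine count (for instance on the log scale) and baseline DBI as covariates. Run the DBI-reduction analysis in patients with baseline DBI above 0. Report any Mann-Whitney or chi-square result as unadjusted and descriptive. In the same edit, reconcile the overall-population wording with Table 1, which collects the rPATD in the intervention arm only.

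The cost is a few lines of text, since the covariates come from data already in Table 1. The DBI-reduction analysis loses patients, but only those who cannot have the outcome. The covariate adjustment was checked by simulation without clusters, so the 4–7% says nothing about the random effect, which is included for consistency with the rest of the plan.

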### Stage II: process evaluation

The process evaluation will aim to evaluate the utility of G-MEDSS in the HMR service from the perspectives of ACPs and patients (or carers), and run alongside (in parallel to) Stage I. Specifically, the process evaluation will obtain the barriers and facilitators to the intervention to understand the factors that may impact on wider implementation (Fig. 4). The process evaluation will be guided by Moore et al.: a mixed-methods descriptive design where quantitative and qualitative data will be collected and triangulated to provide complementary insights of the ACPs and patients (or carers) [55]. Stage II will include both ACP and patient participants (or carers) who were randomised to the intervention arm of the study to evaluate the utility of G-MEDSS in the HMR process.

**Fig. 4 Fig4:**
[figure not shown]
Stage II: Process evaluation of the intervention - flow of patients (or carers) and Accredited Clinical Pharmacists (ACP) through Stage II

#### Recruitment of participants

ACPs who have recruited and completed follow-up of 5–10 patient participants (or carers) will be provided an opportunity to complete and return a feedback survey. The perspective and experiences of patients will be obtained using patient feedback surveys and one-on-one interviews. All patients (or carers) who have consented to participate in the study and have completed the baseline interview will be sent a feedback survey to complete and return.

#### Feedback survey

The ACP feedback survey consists of questions relating to the use of G-MEDSS during medication review and asks ACPs to comment on communicating patient goals of care, anticholinergic and sedative medication use and patient’s attitudes towards deprescribing in medication review reports to the GP. The feedback survey consists of open and closed-ended questions relating to the utility of G-MEDSS overall, is based on a previous study, consists of up to 18 questions, and ACPs will use a 4 or 5-point Likert scale, dichotomous responses and multiple-choice items (with options to provide more detail in free-text responses) to respond [31].

The feedback survey was developed for the patients (or carers) based on a study by Moon et al. using a literature search on existing surveys and interviews with pharmacists to identify relevant topics related to consumer satisfaction with pharmacist-led medication reviews [56]. These were addressing medication related-needs, pharmacist performance for engaging the consumer, and overall satisfaction. The survey consists of 10 questions that use a 4-point Likert scale to respond. Seven additional items designed by the research team will be included to assess patient (or carers) views towards G-MEDSS.

#### Mixed-methods analyses

In order to reduce bias, analyses of Stage II will commence before the analyses of Stage I. An integrated mixed-methods approach will allow for data triangulation and analyses. Data from the feedback surveys will be analysed using descriptive statistics. All patient interviews will be audio recorded and transcribed verbatim. NVivo qualitative data analysis software (QSR International Pty Ltd. Version 12, 2018) will be used for data management and each patient (or carer) participant will be assigned a number for anonymity. The qualitative data will be analysed using a descriptive approach via content analyses. Findings from the feedback surveys and interviews will be triangulated at the interpretation stage and will include discussions with the research team [59].

## Discussion

There is a current need to optimise deprescribing of inappropriate medications in older adults and it is important to involve collaboration with patients within this process [60]. CCDSS for medication management can be considered an effective method for reducing inappropriate prescribing and ADEs in older adults, however there is limited data on the real effect on patient outcomes [61]. Consolidating patient preferences and perspectives on outcomes and goals of therapy is important to guide decisions to reduce or stop medications [62]. There is limited evidence on the effect of goal-directed medication management on prescribing and clinical outcomes. The G-MEDSS is a novel CCDSS intervention that provides clinical decision support for healthcare practitioners, incorporating the patients’ goals and preferences during the medication review process. This study aims to evaluate the implementation of a CCDSS in HMRs to deprescribe medications, and to assess the effect of deprescribing on clinical outcomes.

### Strengths

This study has several strengths. The cluster-randomised trial design is known as the gold-standard study design for evaluating healthcare interventions. Additionally, we have integrated the intervention into usual HMR practice to increase the generalisability of the results, and to allow a more accurate estimation of the intervention’s effectiveness. Finally, the Stage II process evaluation of the study will allow explanation of any discrepancies between expected and observed outcomes, understanding of how context influences outcomes, and may provide insights to aid wider implementation into clinical practice [63].

### Limitations

There are several anticipated limitations within this study. Inherent biases in the sample population of ACPs and patients may affect the results of the study. ACPs usually work independently, therefore it is difficult to recruit ‘clinics’ of ACPs, similar to other cluster-randomised trials that involve general practice clinics. ACPs are also not blinded to the study group, therefore ACPs in the comparison arm may change their behaviour or clinical practice and this may not be reflective of true usual practice. On the other hand, ACPs in the intervention arm may recruit ‘clinically interesting’ patients that may ‘benefit’ from the intervention. To account for and to try to minimise these biases, all ACPs enrolled in the study will be required to undergo training (outlined above). The study is primarily powered to assess whether the intervention will reduce anticholinergic and sedative medication exposure, measured using DBI, after 3 months. It is not powered to assess differences in clinical outcomes, such as physical and cognitive function, even though this data will be captured. Therefore, we may not be able to detect a difference between the intervention and control groups regarding these clinical outcomes. The study will not collect quality of life measures for patients enrolled in the study or economic data on the impact of the intervention.

Regarding the process evaluation, the perspectives of the GPs will not be assessed. This may limit the interpretation of implementation of the intervention in the study and in clinical practice.

